### Procedures

Upon entry into the study (T0, baseline), women in both groups will be asked to complete the Chinese version of the Revised Conflict Tactics Scales (CTS2), Perceived Stress Scale (PSS), Perceived Coping Scale (PCS), and Beck Depression Inventory version II (BDI-II) as well as a demographic questionnaire. Blood samples will be collected from each of the participants by a research nurse trained for this purpose. The intervention group will then receive the qigong intervention. To monitor the self-practice of qigong by participants in the intervention group, we will adopt the recording and monitoring process that was successfully used in the earlier qigong intervention study conducted by our team members [27]. Specifically, each participant will enter on a record card the details of when she practices qigong, for how long, and how many times each day, together with the type and duration of other exercises undertaken in the same day. The participant will be required to submit the record card to our researcher to check the self-practice compliance at the weekly group follow-up sessions. The weekly monitoring will allow the researchers to undertake timely measures to address any early signs of noncompliance. Participants in the wait-list control group will be advised to avoid joining any outside qigong training classes because qigong exercise training will be provided to them after the final outcome measurement. Additionally, to reduce the risk of attrition, the control group will receive monthly health education sessions unrelated to qigong, commencing at the point at which the intervention group starts the weekly group follow-up.

When the intervention group begins the post-training and postintervention periods (T1 and T2, respectively), participants in both groups will complete the CTS2, PSS, PCS, and BDI-II. Blood specimens will be collected from the participants in both groups at T2. When the intervention group has completed the qigong intervention, participants in the wait-list control group will receive the qigong exercise training.

The immediate treatment received by the intervention group, the wait-list control condition received by the control group, and the data collection points is shown in Figure 1.

**Figure 1 Fig1:**
[figure not shown]
**Flow diagram of intervention/wait-list control and data collection points.**

Maintaining minimal attrition throughout the 5.5-month period will be important. Therefore, we intend to use the same field tracking strategies that we used in our previous project [40], which achieved zero attrition. Specifically, we will use systematic field tracking strategies that model the systemized tracking methodology used by McFarlane et al. to achieve a high retention rate [41]. Details of the tracking strategies, which have proven effective in providing early warnings about possible drop-outs, were previously reported [40].

Furthermore, we shall implement the following additional measures to reduce attrition and enhance the participants’ adherence to the intervention:Weekly group follow-up sessions provided by a qigong master to reinforce learning and remedial teaching and motivate the participants to engage in learning and practiceFormation of small subgroups to promote group cohesion and supportElection of a peer leader of each subgroup to enhance group communication and sharingRecording of qigong and other exercises undertaken on a record card, which will be submitted to our researcher at the weekly group follow-up sessions to check each participants’ self-practice complianceMonthly health education talks unrelated to the qigong intervention for participants in the wait-list control groupAll participants will be informed at the time of recruitment and regularly throughout the study that upon successful completion of the project, they will receive a health report based on the data collected as well as a DVD and book on *baduanjin.*

Finally, we will provide an incentive to the participants in the form of food coupons to show our appreciation of their time and efforts.

### Measurements

#### Instruments

The following study instruments with the exception of the C-AAS and demographic questionnaire will be administered at three time points: (a) preintervention (T0, baseline); i.e., upon entry into the study, after randomization but before intervention; (b) post-training (T1, 6 weeks later); i.e., upon completion of the 6-week group learning and practice session; and (c) postintervention (T2, 5.5 months later); i.e., upon completion of the entire qigong intervention program. The C-AAS and demographic questionnaire will only be administered at baseline.The five-item *C-AAS*, which has demonstrated satisfactory psychometric properties [42], will be used to screen potential participants for IPV. If a woman answers “yes” to being emotionally, physically, or sexually abused within the past three years and if the perpetrator is her former or current intimate partner, she is considered to be positive for IPV.The *CTS2*, which has been validated with satisfactory validity and reliability [43], will be used to measure the type and frequency of behaviors used by the perpetrator during partner conflict. This 27-item instrument contains 8 measures of psychological aggression, 12 measures of physical assault, and 7 measures of sexual coercion. How often each behavior occurred within the preceding year is indicated by 0 = not within the past year, 1 = once, 2 = twice, 3 = 3 to 5 times, 4 = 6 to 10 times, 5 = 11 to 20 times, and 6 = 21 or more times.The 10-item *PSS*, the most widely used psychological instrument for measuring the perception of stress [44], will be used to assess the degree to which situations in life have been perceived by the participant as stressful during the past month. The PSS contains six negative and four positive items, and the overall score is obtained by reversing the responses to the four positive items (i.e., 0 [never] = 4, 1 [almost never] = 3, 2 [sometimes] = 2, 3 [fairly often] = 1, and 4 [very often] = 0) and then summing the response scores across all scale items. The PSS score may range from 0 to 40.The *PCS* [45] will be used to assess the types and perceived effectiveness of each of the 13 specific strategies used by the participant in dealing with violence perpetrated by her intimate partner. The strategies may be classified as active or passive; e.g., seeking assistance from family or friends, confronting the partner, redefining the meaning of the situation, or using alcohol or drugs. Scoring is based on a four-point Likert scale: 1 (not at all helpful), 2 (not so helpful), 3 (somewhat helpful), and 4 (very helpful).The Chinese version of the *BDI-II* will be used to assess depressive symptoms experienced within the previous 2 weeks. This 21-item instrument has established construct validity and reliability for Chinese populations [46]. The score may range from 0 to 63, with 0 through 13 indicating minimal depressive symptoms, 14 through 19 indicating mild depressive symptoms, 20 through 28 indicating moderate depressive symptoms, and 29 through 63 indicating severe depressive symptoms.A *demographic questionnaire* will be used to elicit the following information: age of the participant and her partner, education level, place of birth, number of years living in Hong Kong, marital status, duration of the abusive relationship, number of children, employment status of the participant and her partner, financial hardship, receipt of comprehensive social security assistance, need for financial support, and history of chronic illness.

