## Abstract

**Background:**

Abused women, who suffer from chronic psychological stress, have been shown to have shorter telomeres than never abused women. Telomere shortening is associated with increased risk of cell death, and it is believed that adopting health-promoting behaviors can help to increase the activity of telomerase, an enzyme that counters telomere shortening. Qigong is an ancient Chinese mind-body integration, health-oriented practice designed to enhance the function of *qi*, an energy that sustains well-being. Therefore, an assessor-blind, randomized, wait-list controlled trial was developed to evaluate the effect of a qigong intervention on telomerase activity (primary objective) and proinflammatory cytokines, perceived stress, perceived coping, and depressive symptoms (secondary objectives) in abused Chinese women.

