### Randomization and blinding

All eligible participants will be randomized to either the intervention or wait-list control group according to a list of random permutations prepared by block randomization performed by a person not involved in subject recruitment. The block size will be known only by the randomizer. The order of the allocation, which will not be altered, will be centrally controlled to avoid any bias in selection. The research assistants will call the central-control center to obtain the list of random permutations for the allocation.

The questionnaires will be self-completed by the women and numerically coded without revealing the group allocation of the participants. A list of the numerical codes and names of the participants will be kept separately and securely in the central-control center. The researchers conducting the measurement of telomerase activity and its modulating biochemical factors will be blinded to the group allocation.

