#### Primary analysis

The telomerase activity upon completion of the intervention (i.e., T2) between the intervention and wait-list control groups will be assessed by regression analysis with adjustment of baseline values. Residuals will be checked to ensure the adequacy of the method. Additionally, the change in telomerase activity from baseline (T0) to postintervention (T2) will be assessed by a paired t-test. The intention-to-treat principle will be adopted, and all study subjects will be included in the analysis. Missing values will be replaced by the last observed values.

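### Baseline (T0) is taken after randomisation and nothing keeps allocation from the women until it is complete, so the self-reported secondary outcomes can be biased through their own baseline values

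*Protocol article*

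**What the plan says.** - **Timing.** Instruments places T0 "upon entry into the study, after randomization but before intervention". Procedures agrees, because the arms already exist when T0 is collected: "Upon entry into the study (T0, baseline), women in both groups will be asked to complete" the scales, and blood is drawn at the same point.
- **Blinding.** The abstract describes "an assessor-blind, randomized, wait-list controlled trial". Randomization and blinding adds "The researchers conducting the measurement of telomerase activity and its modulating biochemical factors will be blinded to the group allocation", and for the scales "The questionnaires will be self-completed by the women and numerically coded without revealing the group allocation of the participants". Blinding of the women is not claimed.
- **Allocation.** "The research assistants will call the central-control center to obtain the list of random permutations for the allocation". No section says when a woman is told her arm.
- **Use of T0.** Under Primary analysis, T2 telomerase "will be assessed by regression analysis with adjustment of baseline values", and a paired t-test of T0-to-T2 change is added. Under Secondary analysis, the baseline value is a fixed factor in the mixed models for cytokines, PSS, PCS and BDI-II, and changes from baseline are tested by contrasts.
- **Analysis set.** "The intention-to-treat principle will be adopted, and all study subjects will be included in the analysis", with missing values filled by the last observed value.

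**The concern.** A baseline covariate is safe to adjust for because allocation cannot have influenced it. Here the order of events does not guarantee that. With qigong now against qigong later, a woman who has been told her arm knows what she is getting. Numeric coding hides the arm from those who handle the questionnaire, not from the woman who fills it in. If her answers move because of the news, the analysis subtracts part of that movement (adjusted model) or all of it (change score) from the T2 comparison. No later analysis can separate the reaction from a true chance imbalance.

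The order also opens a gap between allocation and first measurement. A woman who leaves in that gap is randomised but has no data, which conflicts with the stated intention to analyse everyone.

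**Working it through.** **1. The plan's own figure.** Sample size gives a difference of 0.075, SD 0.2, 80% power and 5% error. Normal approximation: n = 2 × (1.960 + 0.842)² × 0.2² / 0.075² = 111.6, so 112 per arm. The t-test version gives 112.6, so 113. The stated 113 is reproduced as a two-sided figure. Randomising 240 leaves an allowance of 240 - 2 × 113 = 14 women (5.8%).

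**2. Bias formula.** Let s be the T0 difference (intervention minus control) caused by knowing the allocation.

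- Adjusted effect = (T2 difference) - slope × (T0 difference), so the order of events contributes -(slope × s).
- A change score uses slope 1, so the contribution is -s.

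This treats the mixed model as a baseline-adjusted comparison at one time point. It leaves out any lasting effect of expectation on T2 itself, which any open wait-list trial shares.

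**3. Example on the PSS (assumed slope 0.5, assumed 1-point shift).** The adjusted effect moves by 0.5 × 1 = 0.5 points and the change contrast by 1 point, on a scale of 0 to 40.

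**4. Direction.** Disappointment raises control PSS at T0, and hope lowers intervention PSS at T0. Both make s negative, so -(slope × s) is positive, while the hypothesised PSS effect is negative. The result moves toward no benefit. The same holds for BDI-II, and for PCS with the signs reversed.

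**5. Range in SD units (all assumed).** With equal SDs the slope equals the T0–T2 correlation rho. SE = √(1 - rho²) × √(2/113). The table gives the absolute bias and the two-sided rejection rate when qigong has no true effect.

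| rho | shift 0.1 SD | shift 0.2 SD | shift 0.3 SD |
|---|---|---|---|
| 0.3 | 0.03 SD; 5.6% | 0.06 SD; 7.6% | 0.09 SD; 10.9% |
| 0.5 | 0.05 SD; 7.2% | 0.10 SD; 14.0% | 0.15 SD; 25.6% |
| 0.7 | 0.07 SD; 11.4% | 0.14 SD; 31.4% | 0.21 SD; 59.9% |

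Middle cell: SE = 0.866 × 0.133 = 0.115 and bias/SE = 0.868. The tail on the side of the bias is P(Z > 1.960 - 0.868) = 13.7%. The other tail is P(Z < -1.960 - 0.868) = 0.2%. Under the mechanism in step 4, nearly all of the 14.0% would be findings against qigong.

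**6. Loss before T0.** Telomerase is measured only at T0 and T2, so T0 is the only value that could be carried forward. If T0 and T2 are both absent, nothing can be. The documents give no rate for such loss. At an assumed 2% to 5% of 240, it is 5 to 12 women, and 12 leaves 228 against the 226 required. Power under the plan's assumptions:

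| lost per arm | left per arm | power |
|---|---|---|
| 0 | 120 | 82.8% |
| 7 | 113 | 80.5% |
| 10 | 110 | 79.4% |
| 12 | 108 | 78.7% |

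**The case against.** **Disclosure is not stated.** The text places T0 after randomisation, not after the women are told their arm. A reader might infer that they are known to be unblinded at T0, but no section says so. Collection at the entry visit before disclosure would fit the wording, and the flow diagram is not available to settle it. This stands, and it makes the point conditional. It does not remove it, since nothing in the text protects T0 either.

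**The primary outcome is largely shielded.** A reader might infer that every efficacy model is compromised. The documents do not support that. Telomerase and the cytokines are laboratory assays read by blinded researchers, and no mechanism is given by which hearing one's allocation would move them before any qigong.

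**The scales look back.** The PSS covers the past month and the BDI-II the previous two weeks, which dampens a reaction to recent news without excluding it.

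**The likely bias is conservative.** The raised rejection rates could be read as false claims of benefit. Under disappointment or hope they would be mostly the reverse. That stands, but a diluted secondary result is still a biased one.

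**Early loss may be rare.** Participants must accept random allocation and be available for all testing points. The design is explained before consent, controls are promised qigong later, and the same tracking methods previously gave zero attrition. This stands. How to treat a missing baseline when T2 is present can also be left to an analysis plan.

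**Conclusion.** The order of events is explicit and leaves T0 open to allocation effects. The point holds for the self-reported secondary outcomes, provided that women learn their arm before completing T0. The size is about -(slope × shift) for adjusted effects and -(shift) for change scores. The assumed ranges give 0.03 to 0.21 SD for adjusted effects, but the documents supply neither input, so these figures illustrate and do not estimate. Under disappointment or hope, the direction is toward no benefit.

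For telomerase and cytokines the residual concern is narrow: a woman with neither T0 nor T2 cannot be included, so the commitment to analyse everyone cannot be met for her. A reader might infer a serious loss of power, but the figures show a small one. The primary comparison is not shown to be compromised. This should be fixed because a contaminated or absent baseline cannot be recovered afterwards and the remedy is cheap. It is not a must-fix.

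**What to change.** Amend Procedures and Instruments so that the demographic questionnaire, CTS2, PSS, PCS, BDI-II and the T0 blood draw are completed after consent and C-AAS screening, and before the research assistant calls the central-control center. At minimum, state that the woman is not told her arm until T0 is recorded as complete.

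Reconcile the C-AAS timing in the same amendment. Recruitment uses it after consent to decide enrolment, while Instruments lists it at a baseline defined as after randomisation. Consent and C-AAS already come first under Recruitment, so only the wording in Instruments needs correcting.

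Cost: reordering one visit, a short amendment, and a few T0 assessments and blood samples from women who are then not randomised. The 113 per group and 240 in total do not change. With T0 taken before the allocation call, the allocation-induced T0 shift is zero by design, and every randomised woman has a baseline value. Holding back disclosure alone removes the reporting bias but not the gap for women lost between randomisation and T0.

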
#### Measurement of telomerase activity and its modulating biochemical factors

Previous studies have shown that significant chronic stress-induced changes in telomere lengths cannot be detected over a short period of time, such as 1 to 2 years [26] and that telomerase has multiple telomere-independent and stress-resistant functions [47]. Thus, measurement of the changes in telomerase activity is an optimal alternative and has been successfully performed [26]. The biochemical modulators of telomerase activity include proinflammatory cytokines such as TNF-alpha and IL-6 [48], which are closely related to chronic psychological stress. Elevated levels of inflammation have been observed in IPV survivors [37]. We anticipate that qigong exercise will result in increased telomerase activity, which is associated with decreased levels of the proinflammatory cytokines TNF-alpha and IL-6 in IPV survivors. For each participant in this proposed study, 10 ml of peripheral blood will be collected to measure telomerase activity and TNF-alpha and IL-6 levels at preintervention (T0) and postintervention (T2)in the intervention group as well as before qigong training in the wait-list control group. Peripheral blood mononuclear cells will be isolated for telomerase activity measurement. Telomerase activity will be analyzed using a commercially available kit (*T*elo*TAGGG* Telomerase PCR ELISA; Roche) as previously used by our team members [27]. This method allows for highly specific amplification of telomerase-mediated elongation of products combined with nonradioactive detection following an ELISA protocol. Because this method is PCR-based, it provides a way to perform highly sensitive and quantitative assays of telomerase activities for a large number of samples. This kit has been used in many laboratories worldwide for several years and has resulted in numerous publications, including those in high-impact journals (e.g., Agarwal et al. *Nature*
[49]; Strååt K et al. *Journal of the National Cancer Institute*
[50]; Greco et al*. Stem Cells*
[51]; Ball et al. *Aging Cell*
[52]). Our research team members ([name], Ho) have successfully used this telomerase measurement method to detect significantly greater telomerase activity in mononuclear cells of subjects with chronic fatigue after 4 months of qigong practice than in the control group [27].Finally, the plasma levels of the proinflammatory cytokines TNF-alpha and IL-6 will be measured using commercially available ELISA kits (R&D Systems).

### Data analysis

The primary outcome in this study will be the telomerase level as measured by telomerase activity at postintervention (T2). The secondary outcomes will be the proinflammatory cytokines TNF-alpha and IL-6, perceived stress as measured by the PSS, perceived coping as measured by the PCS, and depressive symptoms as measured by the BDI-II at postintervention (T2).

Data analysis will be performed using Statistical Analysis System software. Each estimated effect will be accompanied by a 95% confidence interval where appropriate. Unless otherwise specified, a 5% level of significance will be used. All statistical methods will be checked for validity before interpretations are made.

The baseline (T0) characteristics between the intervention and wait-list control groups will be assessed by a chi-squared test and Mann–Whitney U test for categorical and continuous data, respectively.

#### Primary analysis

The telomerase activity upon completion of the intervention (i.e., T2) between the intervention and wait-list control groups will be assessed by regression analysis with adjustment of baseline values. Residuals will be checked to ensure the adequacy of the method. Additionally, the change in telomerase activity from baseline (T0) to postintervention (T2) will be assessed by a paired t-test. The intention-to-treat principle will be adopted, and all study subjects will be included in the analysis. Missing values will be replaced by the last observed values.

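### Last-value-carried-forward copies baseline telomerase into the primary T2 outcome, which fixes change at zero for every woman with T0 blood but no T2 blood

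*Protocol article*

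**What the plan says.** All statements are in the protocol article.

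- **Missing-data rule (Primary analysis):** "Missing values will be replaced by the last observed values". The preceding sentence sets the population: "The intention-to-treat principle will be adopted, and all study subjects will be included in the analysis".
- **Primary model (Primary analysis):** telomerase at T2 in the two groups "will be assessed by regression analysis with adjustment of baseline values". In addition, "the change in telomerase activity from baseline (T0) to postintervention (T2) will be assessed by a paired t-test".
- **Blood sampling (Procedures):** at entry, "Blood samples will be collected from each of the participants by a research nurse trained for this purpose". After that, "Blood specimens will be collected from the participants in both groups at T2". At T1 and T2, "participants in both groups will complete the CTS2, PSS, PCS, and BDI-II"; no blood is listed for T1.
- **Telomerase section of Measurements:** this agrees, giving T0 and T2 for the intervention group and a sample before qigong training for the wait-list group. The three-time-point schedule under Instruments covers the questionnaires only.

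The article names no other method and no sensitivity analysis for missing telomerase values.

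**The concern.** With three or more measurements, carrying the last value forward at least uses some post-baseline information. Here it cannot. The only telomerase value that precedes T2 is T0, so a missing outcome is filled with an exact copy of the covariate. In the regression such a woman lies exactly on the line outcome = baseline. In the paired t-test she contributes a change of exactly zero.

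The rule therefore assumes, without saying so, that nobody with a missing T2 sample changed over 5.5 months, in either arm. If that is false, the primary estimate is biased. It is diluted when loss is equal, and shifted in either direction when loss is unequal and telomerase moves over time in both arms. This is a choice the article makes for the primary outcome. It is not a detail left open for an analysis plan.

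**Working it through.** **Inputs from the protocol (Sample size):** SD 0.2; target difference 0.075; 80% power; 5% error rate; 113 per group needed; 120 per group randomised.

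**Inputs assumed:** two-sided test (sidedness is not stated); T0-T2 correlation 0.5; dropout rates other than 5.8%; any common drift; dropout unrelated to the outcome.

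**Step 1: the plan's own figure.** n = 2(1.960 + 0.842)² × 0.2² / 0.075² = 111.6, i.e. 112 per group by the normal approximation. The t-test version gives 112.6, i.e. 113, as stated. The attrition allowance is 1 - 113/120 = 5.8%, or 7 women per arm.

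**Step 2: dilution under equal loss, no drift.** If a fraction d of each arm has T2 replaced by T0, the expected difference is 0.075 × (1 - d). Power at 120 per arm, by the unadjusted formula, is Φ(difference / (0.2√(2/120)) - 1.96). For observed T2 values only, the difference stays at 0.075 and n falls to 120(1 - d).

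| Loss per arm | Expected difference | Power, carried forward | Power, observed T2 only |
|---|---|---|---|
| 5.8% | 0.0706 | 78.1% | 80.5% |
| 10% | 0.0675 | 74.4% | 78.7% |
| 20% | 0.0600 | 64.2% | 73.8% |

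Simulating the baseline-adjusted regression at correlation 0.5 gives the same mean estimates: about 0.071, 0.0675 and 0.060. Adjustment raises power under both approaches and narrows the gap. At 5.8% loss it is 89.3% carried forward against 89.9% for observed values. At 20% loss the fitted baseline slope moves from 0.50 to 0.60.

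**Step 3: interval coverage at 20% equal loss.** The bias is 0.075 - 0.060 = 0.015. The mean nominal SE is 0.0209, and the standard deviation of the estimates across simulated trials is 0.0211. Standardised bias is 0.015/0.0209 = 0.72. Coverage is Φ(1.96 - 0.72) - Φ(-1.96 - 0.72), about 89% instead of 95%. The shortfall comes from the bias.

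**Step 4: unequal loss with common drift, no true effect.** Each arm's mean change is drift × (1 - d), so the spurious difference is -drift × (d_qigong - d_control). With drift -0.10:

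| Loss, qigong / control | Spurious difference | SE | Standardised | False positives |
|---|---|---|---|---|
| 5.8% / 5.8% | 0 | 0.022 | 0 | about 5% |
| 10% / 1.7% | +0.008 | 0.022 | 0.38 | about 6.5% |
| 20% / 5% | +0.015 | 0.022 | 0.69 | about 11% |
| 30% / 5% | +0.025 | 0.021 | 1.17 | about 22% |

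The last column is P(abs(Z + standardised bias) > 1.96). Simulation agrees to within about 2 percentage points. Reversing the arms (5% / 20%) changes the sign to -0.015 with a similar rejection rate. At drift ±0.05 and 20%/5% loss the bias is about 0.007 and rejections are about 6-7%. With no drift the rate stays at 5%, even with unequal loss. Baseline-adjusted regression on observed T2 values stays near 5% throughout.

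**The case against.** **The consequence is small at the attrition the plan expects.** This stands. At 5.8% equal loss the dilution is about 0.004 units, adjusted power falls by less than one percentage point, and the type I error is unchanged. The protocol describes retention measures for both arms and cites an earlier project with no attrition, in which case the rule would never operate.

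**The larger false-positive rates rest on inputs the protocol does not give.** This also stands. A drift of -0.10 is half an SD and exceeds the target difference. Losses of 20%/5% or 30%/5% mean 30 or 42 women missing, against the 14 planned for. These are illustrations and not predictions. Unequal loss is nonetheless conceivable: one arm is asked for 103 hours of practice with record cards, the other for monthly talks while it waits.

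**The comparison favours observed-data regression.** Also true. Dropout was simulated at random, so that analysis is unbiased by construction. The result does not show that it would survive informative dropout, which is why a sensitivity analysis is needed.

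**Two stronger readings are not supported.** A reader might infer that the standard errors are too small because imputed values count as real data. The check does not bear this out: the nominal SE matches the actual spread of the carried-forward estimate (0.0209 against 0.0211). The smaller SE than under observed-data regression (0.021 against 0.025) belongs to a different, shrunken estimator. A reader might also infer that every dropout is scored as unchanged. A woman who stops qigong but gives T2 blood is not imputed, and one without T0 blood has nothing to carry forward.

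**Conclusion.** The point holds: by the protocol's own sampling schedule, the stated rule puts baseline in place of a missing primary outcome and fixes change at zero. The harm depends on how much T2 blood is missing. It is negligible at 5.8% equal loss. At 20% equal loss it is a one-fifth dilution with about 89% interval coverage, and under unequal loss with drift it is a bias of either sign. The dilution figures assume that missing women would have resembled completers. The coverage and false-positive figures also assume a correlation of 0.5, and the false-positive figures assume drift. The documents do not support reading this as a trial whose false-positive rate is already known to be inflated. It should be fixed, because a missing-data rule matters only when data are missing, and this one distorts the primary result in that case.

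**What to change.** Delete the last-value rule for telomerase. State instead a primary baseline-adjusted comparison at T2 that does not fix change at zero and is valid under missing-at-random. Two suitable forms are a likelihood-based model on the T0 and T2 values of all randomised women, or the planned regression with multiple imputation. Either respects intention-to-treat, and the article already plans mixed-effects models for the secondary outcomes. Apply the same principle to the paired change analysis, and add one sensitivity analysis for departures from missing-at-random. The details can sit in the analysis plan.

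The cost is a change of wording and a few lines of SAS code, made before unblinding. The interval will be slightly wider when T2 samples are missing; at 20% loss and correlation 0.5, regression on observed values has an SE of 0.025 against 0.021.
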